### Sample Size and Power Analysis

#### ABC Scale

We anticipate most of our subjects will score in the 50–80 range on the ABC scale at baseline, although we will not exclude those with scores lower than 50. We extracted means and standard deviations (SDs) from published studies involving both community dwelling and home-care facility based older adults (23). Based on these studies, we assume our subjects will have an average score of 60 at baseline with a SD in the 11–20 range. Furthermore, a 12-point change in the scale has been reported to be clinically relevant (27). We anticipate that both the standard therapy and therapist-assisted feedback treatment groups will improve, but the feedback group will score at least 12 points higher on ABC scale at post-assessment. Thus, we anticipate group effect sizes between 0.6 and 1.2 SD for the current study. Type 1 error for the sole primary outcome was set to 0.05. Because we propose to randomize PTs rather than patients, there is clustering inherent in the study design (i.e., cluster-randomization). We account for clustering by computing power based on the effective sample size rather than the actual sample size (28). The effective sample size (ESS = m ^*^ (number of therapists)/DEFF) is based on the design effect (DEFF = 1 + (m – 1) ^*^ ICC), where ICC = intra-cluster (therapist) correlation and m = 50 is the anticipated # patients/therapist. We examined power to detect anticipated changes for a range of ICC between 0.002 and 0.010 [are based on values reported by Killip et al. (28)]. With 200 subjects equally allocated to each of the four therapists (two of which are randomized to therapist-assisted feedback group), the trial is adequately powered (84.3–96.1%) to detect effect sizes between 0.9 and 1.2 SD when ICC = 0,002; effect size of 1.1 SD is detectable with 82.6–91.1% power when ICC is higher (0.10).

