### Statistical Analysis

The analysis will adopt the intent-to-treat strategy. We will estimate and evaluate the difference in the post-assessment ABC between the two treatment groups, adjusting for participants' baseline characteristics (i.e., age, gender, and pathology). Since the outcome of interest is measured at the individual patient level, but PTs are the unit of randomization (i.e., PTs are assigned to either provide feedback in addition to usual care or not), we will fit a linear mixed effects model with post-assessment ABC as the dependent variable; fixed independent effects will be treatment group (therapist-assisted feedback therapy vs. standard therapy) and a random effect term to account for PT variability. The same model will be used to investigate changes on gait speed, our secondary outcome measure. Additionally, we will carry out a sensitivity analysis for those that complete at least 9 (out of 12) sessions to identify whether or not a certain number of sessions influences the observed effects, if any.

An exploratory analysis is proposed including estimating post-intervention differences in other gait metrics collected by the blinded assessor. These secondary gait outcomes will be fit with models similar to the primary outcome measure.

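### The stated ABC power assumes a t-test on 2 degrees of freedom, but neither the power text nor the planned mixed model ties the treatment test to those 2 df

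*Protocol article*

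**What the plan says.** The Statistical Analysis section of the protocol article treats the PT as the unit of randomization. It states "we will fit a linear mixed effects model with post-assessment ABC as the dependent variable", with treatment group as a fixed effect and "a random effect term to account for PT variability". It names no estimation method, reference distribution or denominator degrees of freedom. It says the comparison is adjusted for age, gender and pathology; baseline ABC is not on that list.

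The sample-size section (ABC Scale) states "Type 1 error for the sole primary outcome was set to 0.05" and describes the design as "With 200 subjects equally allocated to each of the four therapists (two of which are randomized to therapist-assisted feedback group"), where "m = 50 is the anticipated # patients/therapist". On method it says "We account for clustering by computing power based on the effective sample size rather than the actual sample size". On the ICC it says "We examined power to detect anticipated changes for a range of ICC between 0.002 and 0.010", and on the effect "we anticipate group effect sizes between 0.6 and 1.2 SD for the current study". The power claim is 84.3-96.1% for effects of 0.9 to 1.2 SD at ICC 0.002. It does not name the test behind these figures.

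**The concern.** With two PTs per arm, the only information on how much PTs differ, apart from treatment, is the difference between the two PTs within each arm. That is 2 df. A t-test that respects this uses a critical value of 4.303; a large-sample test uses 1.96. With so few clusters, the choice of reference distribution can decide the primary result.

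The two sections do not settle that choice. The sample-size text describes an effective-sample-size calculation with no df restriction, yet its figures come from a test that has one. The analysis section names a model that can be tested in several ways, some of which are not the test that was powered. A post hoc choice among them would be open to challenge, and under some of them a chance difference between two pairs of PTs would be called a treatment effect more than 5% of the time.

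**Working it through.** **Inputs** (protocol article, ABC Scale): alpha 0.05; 4 PTs, 2 per arm; m = 50 patients per PT, so 100 per arm; ICC 0.002 to 0.010; anticipated effect d of 0.6 to 1.2 SD. Sidedness is not stated. I assume two-sided, because a one-sided t on 2 df would give 97.3% at 0.9 SD instead of the stated 84.3%.

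**Step 1: reproduce the stated power.**
- DEFF = 1 + (50 - 1) × 0.002 = 1.098, so the effective sample size is 200/1.098 = 182.1.
- Noncentrality = d / √(2 × DEFF/100). For d = 0.9: 0.9/√0.02196 = 6.07. For d = 1.2: 8.10.

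| Reference distribution, ICC 0.002 | 0.9 SD | 1.2 SD |
|---|---|---|
| Stated | 84.3% | 96.1% |
| t, 4 - 2 = 2 df (critical value 4.303) | 84.27% | 96.11% |
| Normal approximation on the effective sample size | >99.9% | >99.9% |
| t with effective sample size minus 2 df | >99.9% | >99.9% |

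Of these, only the 2-df test reproduces the figures. The gait-speed power agrees: under 2 df, 85.7% at ICC 0.005 and 80.5% at ICC 0.01 for 0.12 m/s both imply the same SD, 0.122 m/s.

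**Step 2: what the mixed model does with four PTs.** In a balanced trial let MSB be the between-PT mean square within arms (2 df) and MSW the within-PT mean square (196 df).
- PT-level t-test: t = difference / √(MSB/50), compared with 4.303.
- REML, if MSB > MSW: the PT variance is positive and the statistic is this same t. A z-test compares it with 1.96.
- REML, if MSB ≤ MSW: the PT variance is estimated as zero, MSB is replaced by the pooled mean square on 198 df, and patients are treated as independent. This happens in about 60% of trials at ICC 0.002 and about half at 0.010.

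**Step 3: type I error.** 1,000,000 simulated null trials per ICC, 4 PTs × 50 patients, no covariates, closed-form fits. Figures are good to about 0.1 percentage point.

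| ICC | REML, z | ML, z | PT-level t, 2 df |
|---|---|---|---|
| 0.002 | 4.6% | 5.9% | 5.0% |
| 0.005 | 5.6% | 7.4% | 5.0% |
| 0.010 | 7.1% | 9.7% | 5.0% |
| 0.02 | 9.7% | 13.6% | 5.0% |
| 0.05 | 13.8% | 20.6% | 5.0% |
| 0.10 | 16.4% | 25.3% | 5.0% |

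Only the first three rows lie in the planning range. A likelihood ratio test behaves much like REML with z (4.5%, 5.6% and 7.3% in those rows). A Satterthwaite-type df, which is 2 when the PT variance is positive and 198 when it is zero, gives 3.7% to 7.4% across the six ICCs. Forcing 2 df on the REML fit gives 0.0% to 2.0%, because 4.303 is then also applied to trials whose standard error has already been pooled upwards.

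**Step 4: how different the tests are.** At 0.6 SD, the low end of the anticipated range:

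| ICC | REML, z | t, 2 df |
|---|---|---|
| 0.002 | 94.5% | 57.3% |
| 0.010 | 88.8% | 47.3% |

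**The case against.** The strongest reply is that the large-sample test is the reader's premise. The article specifies a mixed model and no z-test. The df method is commonly left to an analysis plan, which is not shown, and a mixed model can be referred to 2 df. The only evidence in the document about df, the power figures, points towards 2. This stands: a reader might infer that the plan commits to a test with inflated error, and the document does not say so.

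Three further limits also stand.
- At ICC 0.002 the REML z-test holds 5%, and its excess at 0.010 is modest. The 14-16% figures need ICCs of 0.05-0.10, outside the planning range. The article does print 0.10 once, for 82.6-91.1% power at 1.1 SD. But a 2-df test gives 42.4% there, and the printed power range corresponds to ICC 0.015 down to 0.005. That single figure is weak support for expecting a large ICC.
- A Satterthwaite-type df is close to nominal, so not every default analysis fails.
- A reader might infer from 1.96 against 4.303 that z intervals are less than half the proper width. That compares multipliers only. Zero-variance fits raise the standard error, and the mean width ratio is 0.57, 0.55 and 0.53 at ICC 0.002, 0.005 and 0.010.

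The reply does not remove the fault in the stated text. The power method as described does not give the power as stated, and the analysis section leaves open tests whose power at 0.6 SD differs by about 40 percentage points.

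**Conclusion.** The point holds as a mismatch between the power basis and the analysis text. The stated ABC power rests on a 2-df t-test that the sample-size section does not describe, and the Statistical Analysis section does not secure that test. The risk to type I error is conditional. With REML and a z-test it runs from none at ICC 0.002 to about 7.1% at 0.010; with ML it reaches 9.7% at 0.010; it becomes large only if PTs differ more than the plan assumes.

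It does not follow that the first power statement is wrong, since it reproduces exactly under 2 df, or that mixed models are unusable here.

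The figures assume a two-sided test, equal caseloads of 50 per PT, normal outcomes and no covariates.

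**What to change.** 1. Make the primary test a two-stage PT-level comparison. First regress post-assessment ABC on baseline ABC, age, gender and pathology, without treatment arm. Then average the residuals per PT and compare the arms with a t-test and confidence interval on 2 df. Baseline ABC is already collected, so adding it needs no new data.
2. Report the mixed model as supportive only, naming the estimation method and the df method. Do not force 2 df on a REML fit whose PT variance may be estimated as zero, because that is severely conservative (size 0-2%).
3. State in the sample-size section that the power figures assume a two-sided t-test on 2 df. Readers should also see what this implies at the low end of the anticipated effect: 57.3% (ICC 0.002) to 47.3% (ICC 0.010) at 0.6 SD. Reaching 80% power needs 0.84 SD to 0.98 SD.

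This costs wording and no extra patients, and should be settled before unblinded analysis. The downside is wider intervals than a default mixed-model printout, but they are the intervals that the stated power already assumes.

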### Assignment and Blinding

A PT aide who schedules patient appointments assigns each prescreened patient to one of the four PTs who deliver the interventions, depending their open schedule. If a patient is eligible, then he/she undergoes the intervention with the assigned PT. Thus, although the patients are not randomly assigned to each group, this approach was practical for the clinic and avoided selective enrollment assignment since the PT aide assigns an upcoming patient to a PT according to schedule availability without regard to diagnosis, age, or sex. To prevent performance bias, the four treating PTs were distributed into two groups: two PTs provide traditional physical therapy for 100 participants, while the two other PTs provide feedback-based therapy for the other 100 participants. We do not anticipate any selection bias and we do expect equal number of subjects to be assigned to each of the four PTs. Furthermore, information that could introduce bias are withheld from subjects in both groups, i.e., their informed consent does not mention efficacy of feedback-based therapy. To prevent bias due to varying levels of PTs experience, one very experienced PT (>10 years working with patients) and one less experienced PT (<5 years working experience) were assigned to use Mobility Rehab and a similar stratification of experienced and inexperienced PTs were assigned to not use Mobility Rehab. Detection bias is avoided by blinding the PT assistants who administer the pre- and post-assessments and by blinding the investigators and statisticians at OHSU who are analyzing the results regarding subjects' group assignment.

Although we are not assessing blinding by the outcome assessors, the following measures are implemented to avoid assessors from gaining impressions/information about treatment assignment: assessors are based in a different building from the one where the interventions are carried out and, therefore, they do not see patients during rehabilitation sessions and; participants are asked to refrain from mentioning their group allocation to assessors.

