### Interventions

The two rehabilitation interventions for gait disturbances are: (1) standard-of-care physical therapy and (2) therapist-assisted feedback physical therapy. Both groups train twice a week for 6 weeks. Sessions are 45 min long and gait (with or without Mobility Rehab) is trained for 30 min in each session. The additional 15 min include exercises for endurance, strength, and static and dynamic balance in functional tasks. The difference between the two groups is the use of the Mobility Rehab system in the therapist-assisted feedback group. PTs design their own treatment plan for each patient. They are allowed to select modality, overground walking and/or treadmill, and tasks (dual task, head turns, etc.) as appropriate for each patient. During a regular session, patients work on gait with the following tasks for 30 min: weights on ankles, dual tasks, upper extremity support, partial body weight support, speed challenges, direction changes, obstacles, and head turning. The PTs using Mobility Rehab system underwent specific training on how to effectively use the system (e.g., sensors placement, software navigation, selection and interpretation of metrics, etc.) before the start of the trial.

The Mobility Rehab system uses unobtrusive, wearable, inertial sensors with real-time algorithms to provide real-time feedback on five gait metrics: step duration, stride length, arm range of motion, trunk coronal range of motion, and elevation at midswing (Figure 3). Therapists are allowed to select any gait metric and to focus on one or several gait metrics. The visual feedback is provided to a hand-held monitor/tablet (Figure 3) and displayed relative to age-specific normative values, which were previously collected from 120 healthy subjects between the ages of 60 and 89 years during a 2-min overground walk at a comfortable pace. Therapists also can select a minimum and maximum goal for a metric, based on each patient's abilities.

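### The analysis of patients with at least 9 of 12 sessions is given a purpose, judging the influence of session number, that it cannot serve

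*Protocol article*

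**What the plan says.** The Statistical Analysis section states the main strategy plainly: "The analysis will adopt the intent-to-treat strategy". The model for post-assessment ABC has treatment group as a fixed effect, a random effect for therapist, and adjustment for age, gender and pathology.

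The section then adds: "we will carry out a sensitivity analysis for those that complete at least 9 (out of 12) sessions". The aim given for it is "to identify whether or not a certain number of sessions influences the observed effects, if any".

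Two other places bear on this. Under Interventions, the schedule is common to both arms: "Both groups train twice a week for 6 weeks", which makes 2 × 6 = 12 sessions for everyone. Under Assignment and Blinding, the article concedes that "although the patients are not randomly assigned to each group"; patients follow the therapist who has an opening.

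**The concern.** An analysis can speak to the influence of session number only if that number is varied by design, or if patients with different numbers are compared under stated assumptions that make them comparable. Neither is planned. The number completed emerges during treatment, and the analysis keeps one group above one cut-off.

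If the arm difference in that group is larger or smaller than in the full analysis, at least three explanations compete:

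- the number of sessions matters;
- attenders differ in prognosis from non-attenders, and do so differently in the two arms;
- the feedback effect is larger in the kind of patient who attends.

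The stated purpose invites the first explanation. What is at stake is a secondary statement on how many sessions are needed, which a reader could carry into practice. Restricting to attenders also adds a possible selection to a comparison that is already not randomised at patient level.

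**Working it through.** The article states no figure for this analysis, so there is none to reproduce. The check has three parts.

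**1. Is there a contrast in session number?** Interventions gives one schedule for both arms. No section assigns different numbers. Statistical Analysis names one subset (9 or more of 12), with no session-count term, no comparison with patients below 9, and no interaction of arm with sessions. The contrast in the subset is still feedback against standard therapy.

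**2. How large could selection alone be?**

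Inputs:

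- ABC SD of 11 to 20, from the sample size section ("an average score of 60 at baseline with a SD in the 11–20 range"). This is a baseline SD; using it for the post-assessment score is an assumption.
- Share p of an arm reaching 9 sessions: not in the article, assumed.
- Correlation r between tendency to attend and post-assessment ABC: not in the article, assumed 0.3 to 0.5. Read it as what remains after adjustment for age, gender and pathology.
- Session number has no effect on outcome.

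Under a bivariate normal model, the mean of attenders exceeds the mean of the whole arm by

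r × φ(z_p) / p, in SD units, where z_p is the normal quantile of p.

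| p | φ(z_p) | φ(z_p)/p |
|---|---|---|
| 0.9 | 0.1755 | 0.195 |
| 0.8 | 0.2800 | 0.350 |
| 0.7 | 0.3477 | 0.497 |
| 0.6 | 0.3863 | 0.644 |

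With the same r in both arms, the spurious arm difference is r × SD × the difference between the two entries:

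- Equal attendance: 0 points.
- 80% against 70%: 0.497 − 0.350 = 0.147. Lowest: 0.147 × 0.3 × 11 = 0.48 points. Highest: 0.147 × 0.5 × 20 = 1.47 points.
- 90% against 60%: 0.644 − 0.195 = 0.449. Lowest: 0.449 × 0.3 × 11 = 1.48 points. Highest: 0.449 × 0.5 × 20 = 4.49 points.

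With r positive, the arm with lower attendance is flattered, because its attenders are the more selected.

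**3. Does equal attendance remove the problem?** Not always. A simulation (2,000,000 patients per scenario, mean 60, SD 20, 75% attendance in both arms, no effect of session number, a latent prognosis explaining half the outcome variance) gave:

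| Scenario | All patients | At least 9 sessions |
|---|---|---|
| Same selection in both arms, constant effect of 6 | 5.95 | 5.94 |
| Selection on prognosis in feedback arm only, effect 6 | 5.94 | 10.19 |
| Selection in standard arm only, effect 6 | 5.97 | 1.75 |
| Same selection, better-prognosis patients gain more from feedback | 5.99 | 7.16 |
| Selection in feedback arm only, effect 0 | −0.01 | 4.25 |

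The formula agrees. One-sided selection here corresponds to r = √0.5 × √0.5 = 0.5 in one arm and 0 in the other, and φ(z_0.75)/0.75 = 0.3178/0.75 = 0.424, so the shift is 0.424 × 0.5 × 20 = 4.24 points. These one-sided scenarios are deliberately strong. They show direction and possibility, not a forecast.

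**The case against.** The best defence is that this is an ordinary adherence check. It is labelled a sensitivity analysis, it sits behind an intent-to-treat primary analysis, and the phrase about a certain number of sessions may mean no more than the named threshold: does the arm difference hold among patients who received most of the therapy? No decision rule or dose hypothesis is attached. On that reading the subset is acceptable, and asking for a dose-response curve would fault the authors for something they did not propose. This stands as far as the subset goes. It does not rescue the stated aim, because even for the single threshold the analysis cannot tell the influence of sessions from the make-up of those who attend.

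It is also fair to say that the size rests on assumed attendance and correlation, that the planned covariates may absorb some selection, and that both arms have the same schedule and consent forms silent on efficacy. All of this stands.

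A reader might go further and infer three things that the article does not support:

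- **That the subset result will be biased.** It need not be: with equal selection and a constant effect the bias is nil. The subset result by itself does not show which case applies.
- **That patients choose whether to attend, out of motivation or satisfaction.** The article gives no reasons for missed sessions; illness, early discharge or scheduling could act as well.
- **That a bias of 37% of the target is to be expected.** That is 4.49/12, the extreme corner of the assumptions (90% against 60%, r = 0.5, SD 20).

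That a full analysis plan may exist does not answer the point: the purpose is written in the article itself.

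**Conclusion.** The point holds as a fault in the stated purpose. As planned, the 9-session analysis cannot identify whether the number of sessions influences the effect, since that number is not assigned, the subset depends on a post-assignment event, and no contrast across session numbers is named.

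The size is conditional. It is nil with equal selection and a constant effect. With assumed attendance of 80% against 70% and a residual correlation of 0.3 to 0.5, it is about 0.5 to 1.5 ABC points, or 4% to 12% of the 12-point target (0.48/12 and 1.47/12). It is larger if attendance, or the reasons behind it, differ further by arm.

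The consequence is secondary. The primary intent-to-treat comparison is unaffected, and nothing here bears on the trial's answer about feedback against standard therapy.

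**What to change.** In Statistical Analysis:

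1. Replace the stated aim. Describe the analysis as an adherence-restricted supportive analysis of the arm difference in patients completing at least 9 of 12 sessions.
2. Add one sentence that no conclusion about the number of sessions will be drawn from it.
3. Report attendance by arm, for all assigned patients, beside the result.

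Adjusting this analysis for baseline ABC (or baseline gait speed when gait speed is the outcome) would reduce selection on measured factors. Both are already collected at the pre-assessment.

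Inverse-probability weighting of attenders is optional. It cannot correct for unmeasured reasons for attendance, and with about 100 patients per arm, few non-attenders and unrestricted diagnoses, the attendance models could be unstable.

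The cost is some wording, one table and one covariate. Trial conduct does not change. What is given up is a claim about session number that the design could not support.

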## Discussion

This study will determine whether Mobility Rehab is effective for mobility training in older adults with gait disturbances in an outpatient physical therapy clinic setting. We hypothesize that therapist-assisted feedback rehabilitation using Mobility Rehab will be more effective than standard rehabilitation for gait because sensory feedback of performance plays a crucial role in motor rehabilitation. Currently, PTs observe patients' overall walking patterns and provide occasional verbal and/or somatosensory feedback to improve their patients' gait. Although the current approach allows patients to become more aware of how they move so they can correct any abnormal gait strategies, these methods are not optimal. In fact, gait observation is subjective and might be inaccurate, especially for gait impairments that are difficult to observe, such as an excessive trunk motion or reduced foot clearance. An objective characterization of gait impairments is therefore required for accurate patient-specific gait feedback, which may lead to optimized benefits. Additionally, the broad range of patient characteristics (age, gender, diagnosis, mobility condition) in this study will enable the results to be extrapolated to the whole population of elderly patients in need of gait training.

